### Statistical analysis

Success of the randomisation and distribution of outcome measures will be checked before the actual analyses are performed. The baseline characteristics of the non-randomised patients in the cohort are analysed and compared with those of the randomised patients to gain insight into potential selection bias.

The economic evaluation is a cost-utility analysis from the societal perspective (costs per quality adjusted life-year; QALY), based on patients’ reports. A 1-year time horizon will be used, without discounting. Costs related to outcome are analysed using net-benefit acceptability curves, multiple imputation and bootstrapping, including only the uncertainty due to trial sampling error. Cost price analyses are performed for MRI and orthopaedic consultations. Other costs are valued using standard prices (including time involved and travel costs) [24]. QALYs are estimated as the area under the observed 1-year utility curves. Utilities are estimated using the EQ-5D-3 L (primary analysis, Dutch tariff) and the patients’ health VAS, transformed to a utility scale using the power transformation U = 1-(1-VAS/100)^1.61^.

We will evaluate whether MRI referral by GPs is non-inferior compared with usual care in accordance with the clinical guideline, beyond a specified non-inferiority margin (delta) with a defined confidence interval. Non-inferiority of MRI over usual care will be accepted if the upper bound of the 95% CI around the estimated difference in primary outcome (Lysholm Scale) lies below delta. A delta of 4.8 is adopted; this is based on the expected effect in the usual care group as found in our pilot study (see Sample size calculation), and on judgement about the difference between treatments that would be clinically meaningful.

The outcome of both groups are analysed on the basis of the ‘intention to treat’ principle. Linear mixed models with repeated measurements are used to calculate group differences over time. We will adjust for baseline variables that have a clinically meaningful difference between the two groups. In non-inferiority trials, because an intention to treat analysis can increase the type I error (i.e. the risk of falsely claiming non-inferiority), we will also perform a per-protocol analysis [32].

Additionally, we will perform exploratory analysis to identify clinical indicators for better (cost) effectiveness over a 1-year period using univariable and multivariate logistic regression analysis. Different usual thresholds (i.e. 16, 20 and 40 thousand euros per QALY) for the maximum willingness to pay for an extra QALY will be explored.

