**Design and methods:**

This is a multi-centre, open-labelled randomised controlled non-inferiority trial in combination with a concurrent observational cohort study. Eligible patients (aged 18–45 years) have knee complaints due to trauma (or sudden onset) occurring in the preceding 6 months and consulting their GP. Participants are randomised to: 1) an MRI group, i.e. GP referral to MRI, or 2) a usual care group, i.e. no MRI. Primary outcomes are knee-related daily function, medical costs (healthcare use and productivity loss), and quality of life. Secondary outcomes are disability due to knee complaints, severity of knee pain, and patients’ perceived recovery and satisfaction. Outcomes are measured at baseline and at 1.5, 3, 6, 9 and 12 months follow-up. Also collected are data on patient demographics, GPs’ initial working diagnosis, GPs’ preferred management at baseline, and MRI findings.

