### Randomisation and interventions

When patients are eligible for inclusion and have completed the informed consent procedure, the baseline measurement will take place. Hereafter, patients are randomly allocated to the MRI or the usual care group. An independent person produces a randomisation list by computer, using random blocks of 4 and 6. Allocation by one of the researchers ([name] or NS) will be concealed and cannot be influenced or predicted because the randomisation list is not accessible to members of the research team.

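### The economic analysis states no prespecified adjustment for baseline utility, and the only adjustment rule in the article is conditional and of unclear scope

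*Protocol article*

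**What the plan says.** Cost-effectiveness is the first objective in the Aim section of the protocol article. The Statistical analysis section describes a cost-utility analysis over one year and defines the effect measure: "QALYs are estimated as the area under the observed 1-year utility curves". On the source of the utilities it says: "Utilities are estimated using the EQ-5D-3 L (primary analysis, Dutch tariff) and the patients’ health VAS". On method it says: "Costs related to outcome are analysed using net-benefit acceptability curves, multiple imputation and bootstrapping, including only the uncertainty due to trial sampling error". That paragraph names no covariate for the comparison between arms.

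Two paragraphs later, in the text on analysis by randomised group, comes the only adjustment rule: "We will adjust for baseline variables that have a clinically meaningful difference between the two groups". It directly follows the sentence on linear mixed models. Its paragraph opens more broadly: "The outcome of both groups are analysed on the basis of the ‘intention to treat’ principle". Quality of life is listed among the primary outcomes.

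The EQ-5D-3L is on the visit schedule from the start. The abstract says "Outcomes are measured at baseline and at 1.5, 3, 6, 9 and 12 months follow-up", and Table 2 marks the EQ-5D-3L at all six times. The baseline measurement precedes allocation, which is made "using random blocks of 4 and 6"; no stratification factor is mentioned.

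**The concern.** The utility curve begins at a value recorded before randomisation, which MRI referral cannot influence. That value enters the area twice: directly as the first point, and indirectly because patients with better utility at baseline tend to have better utility later. If the arms differ by chance at baseline, part of that difference appears in the incremental QALYs and so in the acceptability curve.

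The conditional rule does not settle this on either reading. If it belongs to the mixed models beside which it stands, no adjustment is stated for QALYs. If it extends to every outcome, adjustment for baseline utility depends on someone judging the observed imbalance in an open-label trial, without a stated threshold. Differences judged too small would be left in, and the precision that adjustment brings would be lost whenever the rule is not triggered. Either way, adjustment for the baseline value is not fixed in advance.

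**Working it through.** The documents give no utility SD, no correlation between baseline and follow-up utility and no expected QALY difference, so there is no stated figure to reproduce. What follows shows the size of the effect under labelled assumptions.

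**Inputs from the protocol article.** Utility at 0, 1.5, 3, 6, 9 and 12 months (abstract; Table 2). 520 patients to be randomised (Sample size calculation), taken as 260 per arm. Thresholds of EUR 20,000 and 40,000 per QALY (end of Statistical analysis; EUR 16,000 is also listed).

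**Assumptions.** Areas computed by the trapezoid rule. Equal SD at all visits. A common correlation rho of 0.3 to 0.5 between any two visits. Utility SD of 0.20, with a range of 0.15 to 0.25.

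**Step 1: weights.** Each interval, as a fraction of the year, gives half its length to each of its ends. The weights are 0.0625, 0.125, 0.1875, 0.25, 0.25 and 0.125, which sum to 1. Baseline has direct weight w0 = (1.5/12)/2 = 0.0625.

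**Step 2: carry-over.** The slope of the area on baseline utility is w0 + (1 − w0) × rho.
- rho = 0.3: 0.0625 + 0.9375 × 0.3 = 0.344
- rho = 0.5: 0.0625 + 0.9375 × 0.5 = 0.531

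So 34% to 53% of a baseline difference is expected to appear in the unadjusted QALY difference. With slopes of follow-up on baseline utility from 0.2 to 0.6, the range widens to 25% to 62.5%.

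**Step 3: size of a chance imbalance.** SE of the baseline difference = SD × sqrt(2/260). At SD 0.20 this is 0.20 × 0.0877 = 0.0175.

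| SD | SE of baseline difference | QALY shift per one SE, rho 0.3 to 0.5 | At EUR 20,000 | At EUR 40,000 |
|---|---|---|---|---|
| 0.15 | 0.0132 | 0.0045 to 0.0070 | EUR 90 to 140 | EUR 181 to 280 |
| 0.20 | 0.0175 | 0.0060 to 0.0093 | EUR 121 to 186 | EUR 241 to 373 |
| 0.25 | 0.0219 | 0.0075 to 0.0116 | EUR 151 to 233 | EUR 301 to 466 |

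Euro figures are per patient. They are the QALY shift times the threshold, before rounding of the shift.

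**Step 4: precision.** In units of the utility variance, Var(area) = S + rho × (1 − S), where S is the sum of squared weights, 0.1953. R² = slope² / Var(area).
- rho = 0.3: Var = 0.1953 + 0.3 × 0.8047 = 0.437; R² = 0.344²/0.437 = 0.27; SE factor sqrt(1 − 0.27) = 0.85, a cut of about 15%
- rho = 0.5: Var = 0.1953 + 0.5 × 0.8047 = 0.598; R² = 0.531²/0.598 = 0.47; SE factor sqrt(1 − 0.47) = 0.73, a cut of about 27%

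This gain does not depend on the SD or on any imbalance being seen. It applies to the QALY difference. The gain for net benefit also depends on the variance of costs, which the documents do not give.

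**The case against.** The strongest reply is that the quoted sentence defines each patient's QALY and does not fix the model that compares the arms. The area under the curve is the dependent variable in an adjusted regression too, and net-benefit curves, multiple imputation and bootstrapping can all be run with covariates. A full analysis plan, not shown, may already contain the term. This stands to the extent that a reader might infer that the plan compares raw areas, and the text does not say so. What remains is that the article does state an adjustment rule, and that rule is conditional, has no threshold and has no stated scope. The point therefore concerns how the rule is fixed, beyond a detail left out.

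A reader might also infer that a baseline imbalance biases the result or passes whole into the QALYs. Neither follows. Under randomisation the unadjusted difference is unbiased over repeated trials, and chance imbalance is part of the sampling error that the bootstrap reflects. Only 6.25% of a baseline difference enters mechanically; the rest depends on a correlation that the documents do not give.

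Finally, a reader might infer that a small imbalance could decide the sign of incremental net benefit. That would need an expected QALY difference, an expected cost difference and the variability of costs. The documents give none of these, so the inference is not supported.

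**Conclusion.** The point holds as a free improvement and not as an error that invalidates the analysis. The article leaves adjustment for baseline utility either unstated or dependent on the observed data. The consequence is lost precision and an estimate that is off target given the imbalance that occurs. Its size rests on the assumed correlation of 0.3 to 0.5 with equal SDs: carry-over of about 34% to 53%, and an SE of the QALY difference about 15% to 27% smaller with adjustment. The euro figures rest in addition on the assumed utility SD. They show scale only and say nothing about which way the cost-effectiveness conclusion would fall.

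**What to change.** Add to the economic paragraph, or to the analysis plan: incremental QALYs are estimated by regression of the area under the curve on randomised arm and baseline EQ-5D-3L utility (baseline VAS utility for the VAS analysis), within each imputed and bootstrap sample and jointly with costs, so that the correlation between costs and QALYs is kept. Incremental net benefit and the acceptability curve are built from these adjusted estimates. The adjustment is made whatever imbalance is observed, and the conditional adjustment rule does not govern this analysis.

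The cost is this wording and one extra model term inside the resampling loop. No new data, visits or patients are needed. If a full analysis plan already specifies the term, it is enough to confirm that the conditional rule does not override it.

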### Outcomes

Patients will fill in questionnaires at baseline and at 1.5, 3, 6, 9 and 12-months follow-up (Table 2). The questionnaires are sent by e-mail which contains a secured hyperlink to the questionnaire. For this purpose the survey application the Lime Survey is used [18].

**Table 2 T2:** Measurement of primary and secondary outcomes

	**Baseline**	**1.5 months**	**3 months**	**6 months**	**9 months**	**12 months**
Primary						
Lysholm	X	X	X	X	X	X
iMCQ/iPCQ	X	--	X	X	X	X
EQ-5D-3 L	X	X	X	X	X	X
Secondary						
KOOS	X	X	X	X	X	X
NRS	X	X	X	X	X	X
GPE	X	X	X	X	X	X
Satisfaction	X	X	X	X	X	X

Lysholm = Lysholm Scale. iMCQ = Medical Consumption Questionnaire from the Institute for Medical Technology Assessment. iPCQ = Productivity Cost Questionnaire from the Institute for Medical Technology Assessment. EQ-5D-3 L = EuroQol 5-Dimensions. KOOS = Knee Injury and Osteoarthritis Outcome Score. NRS = numeric rating scale. GPE = Global Perceived Effect.

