### Sample size calculation

The sample size is based on the Lysholm Scale. In our pilot study, at 1-year follow-up, the effect (Lysholm Scale) of usual care in general practice was estimated at a mean difference of −23 with a standard deviation of 17 (95% confidence interval; CI −27.8; −18.2) [12]. To obtain 80% statistical power with a 2-sided alpha of 0.05, 225 patients per treatment group are required to establish the non-inferiority of MRI referral by the GP compared with usual care within 4.8 points on the Lysholm Scale. Hence, using a 2-sided alpha of 0.05 and 225 patients per group, the trial has a 91% power to detect superiority of MRI referral over usual care assuming a clinically relevant difference of 15% in knee function. Based on previous studies we expect a loss to follow-up of 15%; therefore, the planned trial will require 520 patients with traumatic knee complaints [12,14].

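### Covariates are to be chosen by observed baseline imbalance instead of prognostic strength, so the plan does not secure adjustment for baseline Lysholm

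*Protocol article*

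**What the plan says.** All of the relevant analysis text is in the protocol article, Methods, Statistical analysis. The section opens with a check on the trial's own data: "Success of the randomisation and distribution of outcome measures will be checked before the actual analyses are performed". The effect model is given as "Linear mixed models with repeated measurements are used to calculate group differences over time", and the covariate rule follows: "We will adjust for baseline variables that have a clinically meaningful difference between the two groups". No covariate is named, no size of difference is set, and nobody is named to decide.

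The Outcomes section says "Patients will fill in questionnaires at baseline and at 1.5, 3, 6, 9 and 12-months follow-up", and Table 2 lists the Lysholm at each of these times, so every participant should have a baseline score. The text does not say whether that score is a covariate, one of the repeated outcomes, or neither. The Secondary outcomes section lists eight further baseline characteristics (age and duration of complaints among them), plus the GP's working diagnosis and preferred management.

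The Randomisation and interventions section describes a computer-generated list with random blocks, kept from the research team, with baseline measured before allocation. The non-inferiority decision compares one limit of the 95% confidence interval with the margin: "A delta of 4.8 is adopted".

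**The concern.** With concealed random allocation, a baseline difference between arms is chance by construction. Its size does not show whether adjusting for the variable helps. Adjustment helps when the variable predicts the outcome, and that can be judged before the trial starts. The stated rule uses the wrong criterion and applies it after the arms can be compared.

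Three things are at stake.

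- **Precision.** Baseline Lysholm is probably among the best predictors of later Lysholm. If it enters only when the arms happen to differ, it will usually be left out.
- **Calibration.** An interval whose model depends on the observed imbalance does not have exactly its nominal coverage.
- **Discretion.** With no threshold and about ten candidate variables besides the baseline scores, more than one model could be defended, and one confidence limit decides the trial's claim.

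This is a rule that the article states, so it cannot be set aside as detail left to an analysis plan.

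**Working it through.** **Inputs from the documents.** SD 17 ("with a standard deviation of 17", pilot study), margin 4.8, two-sided alpha 0.05, 225 per group. After 15% loss from 520, 520 × 0.85 / 2 = 221 per group.

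**Assumptions.** The correlation r between baseline and follow-up Lysholm is not given; 0.3 to 0.5 is used, with 0.7 as an outer value. The true difference is zero. The analysis is simplified to one 12-month contrast.

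**The plan's own figure.** The article says "To obtain 80% statistical power with a 2-sided alpha of 0.05, 225 patients per treatment group are required". The standard formula gives n = 2 × (1.96 + 0.8416)² × 17² / 4.8² = 196.9, so 197 per group. With 225, SE = 17 × √(2/225) = 1.603 and power = Φ(4.8/1.603 − 1.96) = 85.0%; with 221, SE = 1.617 and power is 84.3%. The gap between 197 and 225 is a separate matter. Here 84-85% serves as the unadjusted baseline.

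**Always adjusting, if 17 is the SD of the follow-up score.** The SE is multiplied by √(1 − r²).

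| r | SE factor | Power, 221 | Power, 225 |
|---|---|---|---|
| 0.3 | 0.954 | 87.5% | 88.1% |
| 0.5 | 0.866 | 92.9% | 93.3% |
| 0.7 | 0.714 | 98.6% | 98.7% |

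**Always adjusting, if 17 is the SD of change.** The variance is 17² × (1 + r)/2. Power with 225 is 96.0%, 93.3% and 90.1% at r = 0.3, 0.5 and 0.7, against 85.0% for the unadjusted change score.

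**How often an imbalance rule would adjust.** In SD units the baseline difference has standard error √(2/225) = 0.0943. A trigger of 0.1 SD is z = 1.06 and fires in 28.9% of trials. A trigger of 0.2 SD is z = 2.12 and fires in 3.4%. A trigger of 4.8 points, with a baseline SD of 17 assumed, is z = 2.99 and fires in 0.3%. With 221 per group the figures are 29.3%, 3.5% and 0.3%.

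**Power under a fixed trigger (17 as the follow-up SD, r = 0.3 to 0.5).** At 0.2 SD power stays at about 85-86%, so nearly all the gain is lost. At 0.1 SD it is about 86-89%.

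**Two-sided error under a fixed trigger.** When the rule fires, the adjusted estimate is independent of the baseline difference and has error 5%. When it does not, the unadjusted test is used in trials already known to be balanced, where it is conservative. With k the trigger as a z value:

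error = 0.05 × P(|Zx| > k) + P(|Zy| > 1.96 and |Zx| < k), where corr(Zx, Zy) = r.

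For r = 0.5, 225 per group:

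- 0.1 SD: 0.05 × 0.289 + 0.0224 = 3.7% (simulation runs scatter from 3.5% to 4.0%)
- 0.2 SD: 4.5%
- 4.8 points: 4.9%

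**Error if the better of two results were chosen.** The adjusted and unadjusted statistics have correlation √(1 − r²). The chance that at least one exceeds 1.96 at the margin is 3.2%, 3.7% and 4.1% at r = 0.3, 0.5 and 0.7, instead of 2.5%. A simulation with estimated variances gave 3.3%, 3.8% and 4.2%.

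**The case against.** Four points deserve weight.

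1. **Baseline may already be in the model.** Table 2 counts baseline among six Lysholm measurements, and the model uses repeated measurements. If baseline is one of the outcomes, with a common mean across arms, most of the precision is recovered whatever the imbalance. A reader might infer that baseline Lysholm certainly enters only when the arms differ; the article does not settle that. The precision loss is therefore conditional, and the imbalance rule would still govern every other covariate.

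2. **The SD is ambiguous.** The Sample size calculation attaches 17 to a mean difference at one year, which looks like a change within patients. Then at r = 0.3 the follow-up SD is 17/√(2 × 0.7) = 14.4, and a comparison of follow-up scores alone has about 94% power, against 96% with adjustment. The gain depends on a comparator that the article does not state.

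3. **The miscalibration is conservative.** A reader might infer from incorrect coverage that false non-inferiority becomes more likely. Under any fixed trigger it becomes less likely, and at triggers near the margin the distortion almost disappears.

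4. **Choosing by result is not proposed.** The criterion is baseline difference, and the check on randomisation comes before the outcome analyses. Baseline precedes allocation, so open-label treatment cannot bias it. A reader might infer that the plan itself inflates the error rate; the text does not support that. An undefined threshold leaves room for it and no more.

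All four limit the size of the problem. None of them makes imbalance a sound criterion.

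**Conclusion.** The point stands as a weakness in a stated rule that should be corrected. It does not invalidate the trial. Choosing covariates by observed imbalance has no statistical basis under concealed randomisation, and the rule as written names neither a variable nor a threshold.

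Unless baseline Lysholm is already a constrained repeated outcome, the rule forgoes most of a gain of about 3 to 8 percentage points of non-inferiority power when 17 is the follow-up SD and r is 0.3 to 0.5. If 17 is the SD of change, the gain over an unadjusted change score is about 8 to 11 points (85.0% to 93.3% or 96.0%).

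The effect on the interval is small and conservative: 3.7% two-sided error at a 0.1 SD trigger with r = 0.5, and close to 5% at larger triggers. One-sided error of about 3-4% arises only if the open threshold is used to select the more favourable model. All sizes rest on an assumed correlation and on a single-time-point simplification of the mixed model.

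**What to change.** Replace the covariate sentence in Statistical analysis with:

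> The mixed model for the Lysholm score includes baseline Lysholm in all analyses, irrespective of observed balance, either as a fixed covariate or as a repeated outcome with the baseline mean constrained equal across arms; any further prognostic covariates are named before allocation-level data are seen.

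Do the same for the KOOS and NRS pain, each with its own baseline, and delete the imbalance criterion. Baseline tables can still describe the groups, but should not select the model.

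The cost is one sentence in the protocol and the analysis plan. Baseline scores are already scheduled, so no extra patients, visits or measurements are needed.

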## Discussion

Although GPs in the Netherlands increasingly refer patients with knee complaints to MRI, there is lack of evidence regarding whether or not this is cost-effective care. We have reported the design of a non-inferior RCT to investigate the cost-effectiveness of MRI on referral of the GP compared with usual care, in patients with traumatic knee complaints.
